## Abstract

**Background:**

Mobile app–based therapies are increasingly being employed by speech-language pathologists in the rehabilitation of people with aphasia as adjuncts or substitutes for traditional in-person therapy approaches. These apps can increase the intensity of treatment and have resulted in meaningful outcomes across several domains.

**Objective:**

VoiceAdapt is a mobile therapy app designed with user and stakeholder feedback within a user-centered design framework. VoiceAdapt uses two evidence-based lexical retrieval treatments to help people with aphasia in improving their naming abilities through interactions with the app. The purpose of the randomized controlled trial (RCT) proposed here is to examine the feasibility and clinical efficacy of training with VoiceAdapt on the language and communication outcomes of people with aphasia.

**Methods:**

A multicenter RCT is being conducted at two locations within Canada. A total of 80 people with aphasia will be recruited to participate in a two-arm, waitlist-controlled, crossover group RCT. After baseline assessment, participants will be randomized into an intervention group or a waitlist control group. The intervention group participants will engage in 5 weeks of training with the app, followed by posttreatment and follow-up assessments after an additional 5 weeks. Those in the waitlist control group will have no training for 5 weeks; this is followed by pretreatment assessment, training for 5 weeks, and posttreatment assessment. All trial procedures are being conducted remotely given the COVID-19 pandemic.

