### Study Design

The RCT will have a two-arm, randomized, waitlist-controlled, crossover group design. In Phase 1, people with aphasia randomized to the intervention group will train with VoiceAdapt. The control group will be a waitlist treatment-deferred group. In Phase 2, the control group will train with VoiceAdapt (see Figure 1). Participants will be randomized to groups according to a computer-generated randomization list.

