### Duration

The participants will take part in the study for approximately 13 weeks once enrolled. Pretreatment assessment will take place in Week 1, followed by 5 weeks of engagement in Phase 1 (treatment or control). Midpoint assessments will take place in Week 7, followed by 5 weeks of engagement in Phase 2 (crossover into control or treatment). Final assessments will take place in Week 13 following study enrollment.

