### Sample Size Determination

The planned enrollment for the study is 80 (ie, 40 at each of the two sites in Canada). The sample size calculation is based on the medium effect sizes estimated in our study according to previous results. Accounting for a dropout rate of approximately 10%, we need to include 79 people with aphasia; thus, we plan to enroll 80 people with aphasia. We will conduct an intention to treat analysis and include all the randomized participants in our analyses.

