### Analytic Strategy

Mixed-effects regression will be used to analyze the 2 × 2 crossover trial with one baseline [31]. The analysis will include covariate adjustments for variables such as the recruitment site and participant characteristics (eg, sex, age, hours of training, assessors, and caregiver characteristics). Adjustment can increase the precision of the treatment effect estimates and confirm whether training was equally efficacious across covariates (ie, using covariates by treatment interaction) and whether the retention of improvement was equal across covariates (ie, covariates by carryover interaction). Mixed-effects regression can also account for hierarchical sampling, which is important if participants within sites are more similar than if they were randomly chosen. If carryover is detected, we will also estimate the treatment effects after excluding the Period 2 assessments affected by carryover.

The Mauchly test will be used to evaluate whether the sphericity assumption is tenable. If the variances are unequal, we will disaggregate the analysis and use paired and two-group *t* tests as appropriate to estimate the treatment, carryover, and period effects; if covariate adjustment is required, these contrasts will be evaluated using mixed-effects regression while also accounting for hierarchical sampling.

Interim analyses will be conducted when quarterly enrollment targets are met (ie, 20, 40, and 60 participants).

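### The plan reads retention from the carryover term, but with a delayed follow-up in one arm only, that term equals retention only if the app works equally well in both phases

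*Protocol article*

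**What the plan says.** The abstract (Methods) gives the two arms different visits after training. For the intervention arm: "The intervention group participants will engage in 5 weeks of training with the app, followed by posttreatment and follow-up assessments after an additional 5 weeks". For the waitlist arm: "Those in the waitlist control group will have no training for 5 weeks; this is followed by pretreatment assessment, training for 5 weeks, and posttreatment" testing.

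The Duration section puts assessments for both arms in Weeks 1, 7 and 13 and ends there: "Final assessments will take place in Week 13 following study enrollment". The Study Design section confirms what the comparator is doing in the second half: "In Phase 2, the control group will train with VoiceAdapt".

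The Analytic Strategy section plans a mixed-effects analysis of a 2 × 2 crossover with one baseline. Among the purposes of covariate adjustment it lists establishing "whether the retention of improvement was equal across covariates (ie, covariates by carryover interaction"). If carryover is found, treatment effects are also to be estimated without the affected Period 2 data.

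**The concern.** The parenthesis in the Analytic Strategy section treats carryover and retention as the same quantity. In this schedule they are not.

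Week 13 is the only visit that follows a training-free interval, and only the intervention arm has had one. The waitlist arm has just finished training at that visit, so the Week 13 difference between arms sets a retained effect against a fresh one. Turning that difference into retention requires knowing the fresh effect. The crossover model supplies it by assuming that the effect is the same as in Phase 1.

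That assumption may fail. Training is self-directed home practice with weekly check-ins, and one arm starts after 5 weeks of waiting. If the waitlist arm responds less or more than the intervention arm did, the gap passes one for one into the carryover term and would be reported as better or worse maintenance. A covariate related only to the Phase 2 response would appear as a difference in retention.

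**Working it through.** **Inputs.** Visits and training status come from the abstract and the Study Design and Duration sections. Enrolment is 80. The stated need is: "Accounting for a dropout rate of approximately 10%, we need to include 79 people with aphasia". The dropout step is consistent: 71 / 0.90 = 78.9, rounded up to 79. The 71 cannot be rebuilt from the article, and nothing here depends on it. The allocation ratio is not stated, so 1:1 is assumed: 80 × 0.90 = 72 completers, 36 per arm. All effect sizes and correlations below are assumptions.

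**1. Expected means.** Let m be the common baseline mean, p1 and p2 the period or repeat-testing shifts at Weeks 7 and 13, t1 and t2 the app effects in Phases 1 and 2, and L the effect retained 5 weeks after training.

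| | Week 1 | Week 7 | Week 13 |
|---|---|---|---|
| Intervention | m | m + p1 + t1 | m + p2 + L |
| Waitlist | m | m + p1 | m + p2 + t2 |

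**2. Carryover term.** The between-arm differences are t1 at Week 7 and L − t2 at Week 13. Carryover is their sum:

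t1 + (L − t2) = L + (t1 − t2).

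Baseline adjustment subtracts a multiple of the baseline difference, whose expectation is zero under randomisation, so the result does not change.

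**3. Is the alias in the design or in the model?** Six cell means depend on six parameters (m, p1, p2, t1, t2, L), and the design matrix has rank 5. Raising p2 by 1 while lowering t2 and L by 1 each leaves every mean unchanged. No parameterisation of these visits separates L from t2 without an added assumption.

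**4. Size in Boston Naming Test points,** with t1 = 4 and true L = 2 unless shown:

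| Phase 2 effect t2 | Carryover term | As share of t1 | True share |
|---|---|---|---|
| 4 | 4 + 2 − 4 = 2 | 50% | 50% |
| 3 | 4 + 2 − 3 = 3 | 75% | 50% |
| 2 | 4 + 2 − 2 = 4 | 100% | 50% |
| 5 | 4 + 2 − 5 = 1 | 25% | 50% |
| 3, with L = 0 | 4 + 0 − 3 = 1 | 25% | 0% |

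**5. The planned use, the covariate interaction.** Take two subgroups, both with t1 = 4 and L = 2. If t2 is 4 in one and 3 in the other, the carryover terms are 2 and 3. The interaction is 1 point although retention is identical.

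**6. Against sampling error.** In SD units, with 36 per arm and compound-symmetric correlation of 0.5 to 0.9, the carryover term has a standard error of 0.33 down to 0.18. With t1 = 0.5, t2 = 0.3 and L = 0, it estimates 0.2 at every correlation. That bias is of the same order as the standard error and does not shrink with sample size. The treatment effect estimated alongside it stays at 0.5, which is the Phase 1 effect.

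**7. What the existing visits do give.** The intervention arm's Week 7 to Week 13 change is L − t1 + (p2 − p1): loss since the end of training, plus drift. The waitlist arm's Week 1 to Week 7 change is p1, which is drift without training. Subtracting gives L − t1 + (p2 − 2p1), which is L − t1 if drift is equal in the two intervals (p2 − p1 = p1). Under the same condition, the waitlist arm's Week 7 to 13 change minus its Week 1 to 7 change is (t2 + p2 − p1) − p1 = t2, so equality of t1 and t2 can be examined.

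**The case against.** The strongest reply is that retention is peripheral. It is not a stated objective or a listed outcome, the conclusions make no maintenance claim, and the word appears once, as a purpose of covariate adjustment. This stands and limits the importance of the point. The percentages above illustrate the alias and are not figures the plan promises to report. The sentence is still an affirmative statement of what the interaction will show, and a fuller analysis plan cannot make it true for these visits.

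Second, one-sided follow-up is inherent in a waitlist crossover, and the plan protects efficacy by re-estimating without Period 2. That is also true. But dropping Period 2 removes the only follow-up data, so it does nothing for retention.

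Third, hours of training is a planned covariate and the app logs training time. This addresses one cause of unequal effects, the amount of practice. It does not cover a different response to the same hours.

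Fourth, the within-arm change rests on an assumption too, because drift shifts it one for one while the crossover term removes drift. This stands, and the estimate should be reported with that limit stated.

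Three stronger readings are tempting and not supported. A reader might infer that the waitlist arm is never seen after training; it has an immediate posttreatment visit and lacks only a delayed one. A reader might infer that equal effects can never be checked; step 7 shows a check that needs one assumption. A reader might infer that the efficacy result is compromised; the randomised Week 7 comparison involves neither L nor t2.

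**Conclusion.** The point holds for the retention analysis only. Under the documented schedule the carryover term is L + (t1 − t2), so it and its covariate interactions measure retention only if the app effect, and its dependence on the covariate, is the same in both phases. Any departure enters one for one: with the assumed values, a true retention of 2 points reads as anything from 1 to 4.

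The algebra rests on the visit schedule alone. The sizes rest on assumed effects, and the count of about 40 people followed up (about 36 after dropout) rests on assumed 1:1 allocation. The concern is moderate: a subsidiary analysis carries a label that the design does not support, and correcting it is cheap.

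**What to change.** In the Analytic Strategy section:

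- Stop describing the carryover term or its covariate interactions as retention. Describe them as carryover aliased with a treatment-by-period difference.
- Report maintenance as the intervention arm's Week 7 to Week 13 change with a confidence interval, and examine covariate associations on that change. State that it has no concurrent untrained control and includes repeat-testing effects.
- As a sensitivity check, subtract the waitlist arm's untrained Week 1 to Week 7 change, with the equal-drift assumption written out. That assumption could fail if the gain from repeat testing differs between the first and second retest.

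All of this uses visits already scheduled. The cost is wording, a small additional analysis and a more modest claim about maintenance. An extra delayed visit for the waitlist arm is not needed: it would observe follow-up in both arms, but with no untrained group after Week 7 the alias would remain (rank 7 for 9 parameters).

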**Results:**

Recruitment of participants started in September 2020, and the study is expected to be completed by March 2022. Publication of results is expected within 6 months of study completion.

**Conclusions:**

The results of the RCT will provide information on evidence-based practice using technology-based solutions to treat aphasia. If positive results are obtained from this RCT, the VoiceAdapt app can be recommended as an efficacious means of improving lexical retrieval and communicative functioning in people with aphasia in an easily accessible and a cost-effective manner. Moreover, the implementation of this RCT through remote assessment and delivery can provide information to therapists on telerehabilitation practices and monitoring of app-based home therapy programs.

**Trial Registration:**

ClinicalTrials.gov NCT04108364; https://clinicaltrials.gov/ct2/show/NCT04108364

**International Registered Report Identifier (IRRID):**

DERR1-10.2196/30621

## Introduction

### Background

Aphasia is an acquired language disorder, most commonly caused by stroke. It can impact linguistic expression and comprehension in written and oral modalities. As such, this condition can have devastating consequences on the social, emotional, and occupational functioning of people with aphasia [1]. Although aphasia affects nearly one-third of all individuals who experience a stroke [2,3] and has been associated with poorer outcomes in the acute and chronic periods following stroke [4], the condition itself remains relatively unknown among the general public [5].

Rehabilitation for people with aphasia provided by speech-language pathologists (SLPs) has shown improved outcomes [6,7]. However, several factors, including constraints on health care resources, often prevent people with aphasia from receiving services, particularly in the chronic stages. The recent proliferation of mobile app–based therapies (apps) has provided a cost-effective means by which people with aphasia can receive prolonged rehabilitation. SLPs have been increasingly employing such apps as adjuncts or substitutes for traditional (in-person) therapy approaches, with meaningful outcomes observed across several domains [8,9]. Such apps have the potential to increase the intensity of rehabilitation, a factor that is associated with greater long-term recovery [10-12]. Moreover, recent evidence has shown that people with aphasia can self-deliver this type of intervention and attain positive language and communication outcomes [13-15]. Technology also enables measuring multiple parameters of user interactions with touch-based devices, and algorithms can be deployed to adapt content based on the user/patient state.

Large-scale randomized controlled trials (RCTs) investigating the clinical utility of tablet-based speech-language therapy apps for aphasia have not been conducted. Nevertheless, preliminary evidence on the utility of app-based therapy for adults with acquired aphasia is emerging. Mallet and colleagues [16] demonstrated that mobile tablet–based rehabilitation is feasible for delivering speech-language therapy in an acute care setting. In this study, patients with communication deficits following acute stroke interacted with tablets containing commercially available speech-language therapy apps. The participants in this study expressed a desire to be more active in their rehabilitation, and they even exceeded the minimum time (one hour per day) recommended for engaging with the mobile tablet. In a more recent RCT conducted on 32 people with aphasia, Braley and colleagues [13] reported that people with aphasia in the treatment group who practiced a variety of speech, language, and cognition exercises using a tablet-based therapy app (ie, Constant Therapy) demonstrated greater language outcomes than a group who completed worksheet exercises. Importantly, this RCT was conducted virtually with participants self-managing their participation through periodic monitoring by the researchers. Additional evidence derived from case series and small group studies also proves the utility of app-based therapy for adults with aphasia in the chronic stages. Participants in these studies have shown improvements across a variety of outcome measures, including naming of trained and untrained items, standardized language and cognitive assessment batteries, and spoken discourse [15,17-19].

Despite the increasing availability of therapy apps designed for aphasia [20], very few have been designed with inputs from relevant stakeholders following the principles of user-centered design (UCD). UCD is a systematic approach to meet usability and user experience goals through integrating the needs and abilities of users during the design process of an artifact. This ensures that the product/service design and development align with all the relevant stakeholders’ needs (ISO 9241-220). Essential UCD activities include planning and managing the process, defining the context of use for each user group, gathering user and stakeholder requirements, designing an ergonomic solution based on the requirements, and evaluating the design within a user-centered approach [21].

In a recent review, only three apps were identified where developers engaged people with aphasia in the design process [22]. All these apps engaged patients to varying extents during therapy evaluation or prototype testing. There was no evidence of patients being involved in either of the two initial phases of app development (ie, theory-based conception, software implementation). Based on the above review, the authors present a broad, four-phase model of the app development process encompassing the following: (1) theoretical considerations, (2) software development, (3) pilot testing, and (4) long-term evaluation. The authors conclude that people with aphasia should be involved in all phases during the development and evaluation of therapy apps, as their involvement could “enhance the product quality, functionality and acceptability, and increase patients’ motivation to use these digital therapies” [22].

### VoiceAdapt

Recently, the VoiceAdapt Consortium (VC), an international team of researchers from the fields of computer science, usability design, and speech-language pathology, has produced an app for treating naming impairments in people with aphasia. Using evidence-based lexical retrieval protocols, the VoiceAdapt app instantiates Phonological Components Analysis (PCA) [23] and Semantic Feature Analysis (SFA) [24] into an adaptive, voice-responsive therapy app that people with aphasia can use to improve their naming skills.

The VoiceAdapt project has so far involved 75 end users (people with aphasia, clinicians, and caregivers) in the UCD process to identify the main barriers and obstacles to app-based training and rehabilitation; ensure independent usage and sustained motivation; and optimize the end-user experience and training impact. This was achieved by eliciting user requirements (conducting guideline-based structured interviews), designing solutions (mock-ups, prototypes), and evaluating the designs against the requirements (focusing on user experience in terms of multimodal speech interaction and adaptivity) over three iterative cycles. The result is a mobile speech-language training app for people with aphasia that can run on iOS and Android platforms. The app supports regular training sessions, adaptivity (individual performance thresholds for training material selection), personalization (training content is selected based on individual interests), and coordination between therapists and patients; it also addresses multimodal language goals (reading, understanding, and production).

### Study Purpose

The purpose of this study is to examine the impact of the VoiceAdapt adaptive speech-language treatment app, created using the principles of UCD, on the naming abilities of people with aphasia within an RCT. Secondary outcomes focusing on overall language improvement, communication, and quality of life will also be examined. Herein, we present the protocol of the VoiceAdapt study (ClinicalTrials.gov NCT04108364).

## Methods

### Selection of Communities for the Study, Participants, and Procedures

Participants will be recruited from two geographic regions in Canada through the Language Sciences Lab (Department of Speech-Language Pathology, University of Toronto) and Aphasia Research Lab (Department of Communication Sciences and Disorders, University of Alberta), based in Toronto, Ontario and Edmonton, Alberta, respectively. Participants with aphasia will be recruited from community-based aphasia centers and programs, clinics, and research databases. Initial contacts will be made with aphasia centers and programs providing information about the study, followed by recruitment presentations and meetings with interested participants.

### Inclusion and Exclusion Criteria

The participants enrolling in the study will meet the following inclusion criteria: be at least 6 months post the onset of a stroke in the left hemisphere; have mild-to-moderate aphasia (Aphasia Quotient ≥30 on the Western Aphasia Battery-Revised [WAB-R]) [25]; score below 75% correct on the Boston Naming Test (BNT) [26] during initial assessment; exhibit prominent verbal expression impairment; pass screenings for vision, hearing, and basic cognitive functioning; speak English as a primary language; and be willing to commit to participation for the entire study duration. Despite meeting all these inclusion criteria, participants will be excluded if they are currently engaged in individual (one-on-one) speech-language therapy or are using speech-language therapy apps.

### Study Design

The RCT will have a two-arm, randomized, waitlist-controlled, crossover group design. In Phase 1, people with aphasia randomized to the intervention group will train with VoiceAdapt. The control group will be a waitlist treatment-deferred group. In Phase 2, the control group will train with VoiceAdapt (see Figure 1). Participants will be randomized to groups according to a computer-generated randomization list.

**Figure 1 figure1:**
[figure not shown]
Schematic of the study design.

### Intervention

The app intervention comprises naming exercises based on evidence-based anomia treatments, SFA and PCA, delivered on a mobile tablet. The exercises involve the presentation of a colored picture and a series of prompts designed to engage the people with aphasia in providing semantic features (eg, “What is it used for?” [action]; “What does it look like?” [properties]); or phonological components (eg, “What sound does it start with?” [first sound]; “What is a rhyming word?” [rhyme]). Figures 2 and 3 display summary screens reviewing the generated semantic and phonologic features of the target items, respectively (Additional screenshots of the app are displayed in Multimedia Appendix 1). A help screen also reminds users of the various features (Figure 4). The patient’s voice is recorded and used as the input for the app. The app is designed to maximize user engagement through UCD principles. People with aphasia randomized to the VoiceAdapt treatment group will be instructed to practice using the app during weekdays for one hour per day for 5 weeks. The people with aphasia will have the option of downloading the app on their own tablets from a link provided by the researchers, or the researchers will provide them with tablets with the app loaded. Research staff will check in and monitor progress through email or telephone/video calls on a weekly basis.

